### Recruitment

A total of 60 practices will be recruited. Assuming an average practice size of 5 GPs, we estimate around 160–200 GPs and Nurse Practitioners will take part. The aim is to recruit all these practices in the first 6 months of the study. Due to the nature of the intervention, practices must be adequately computerized and participants will have to work at least 5 clinical sessions per week to take part in the STAR Educational Program. We will attempt to recruit at least two thirds of the prescribers at each practice. This is due to the nature of the analysis and the feedback provided on an individual and practice level. Practices who submit samples to laboratories that are not part of the DataStore system will be excluded from the study. GPs and nurse practitioners in Wales will receive an invitation letter, information sheet, personalized consent form, return envelope, and a flyer on the study. Additionally, letters to practice managers will be sent to alert them to the study.

### Randomization

Randomization will take place once all practices have been recruited in order to obtain an allocation with near optimal balance for total annual antibiotic prescribing averaged over the past three years (PARC), practice size (number of whole time equivalent staff at recruitment) and proportion of GPs in the practice registered for the study. Practices will be sub-divided into three blocks and allocation balanced within each block[51,52]. All possible allocations within a set will be estimated and the balance statistic based on the sum of the squares of the differences between each group on each measure (standardized). The 1000 possible allocations within each set with the best balance will be selected and passed to an independent statistician and one allocation will be selected at random. Once the final allocation to two groups has been selected for each set of practices, this independent statistician will randomly allocate intervention or control to the two groups.

### Trial procedures

The STAR Program will be delivered to intervention practices within the first study year, and then offered to control practices after the follow-up is complete. Practices will be followed up one year after the intervention.

### Process evaluation

We will conduct a process evaluation in which we:

1. Explore participation in the seminars and use of software supported learning and map the clinicians' use of the system (how often they log in, which pages they use) in relation to the primary outcome.

2. Complete qualitative interviews with one clinician from each participating intervention practice to explore ongoing use of the prescribing and resistance data, the website, the communication skills, and the acceptability and perceived usefulness of various components of the intervention. Clinicians from intervention practices will be purposively sampled for interview based on gender, experience, antibiotic prescribing, practice setting and when they completed the training. Interviews will continue until all the themes are saturated, previous experience suggests that this will be around 30 interviews[35,38,53]. The interviews will be conducted over the telephone and audio recorded. The interviews will be transcribed for later analysis.

### Health economics evaluation

We will also undertake a cost effectiveness analysis from an NHS perspective. Direct costs/savings will include the cost of the STAR Program, potentially longer consultations in intervention practices and potentially fewer antibiotics dispensed. Indirect costs/savings will include differences in antibiotic adverse events, re-consultations for the same illness and complications of common infections including hospital admissions. All resource use will be monitored prospectively. Since this is a 'complex intervention', no attempt will be made to examine the cost effectiveness of each specific component. Prospective monitoring of health service resource use, however, will identify the cost of each element of the intervention. The different elements will also be examined in the qualitative study. Education represents a one-off cost which may produce a stream of benefits over time. Accordingly, the costs of education can be dealt with similarly to capital equipment with costs expressed on an Equivalent Annual Cost (EAC) basis[54]. Length of consultation will be estimated using facilities in existing practice computer systems in a sample of practices.

The study has been approved by the Multi-centre Research Ethics Committee (MREC 06/MRE09/31) and all Local Health Boards (LHBs) in Wales.

### Analysis

#### Main analysis

The main analysis will be intention to treat and will compare the two groups for annual total antibiotics dispensed per 1000 practice patients within practices in the year following the intervention, using analysis of covariance with the average of the previous three years' prescribing as a covariate. Secondary outcomes of average hospital admission rates for specified complications, antibiotic resistance rates will be similarly compared between the two groups for the whole year. A comparison will be made between groups for complications managed in primary care, re-consultations and further consultations for a similar illness, using summary data extracted from practice computer systems, for a subset of practices. Exploratory analyses will use analysis of covariance to adjust for practice factors that might plausibly influence outcomes. Weighted average Townsend scores for each practice will be used to examine socio-economic influences on prescribing. The degree of uptake of the intervention will be used in further exploratory models to explore impact on outcomes. Antibiotics dispensed for intervention and control practices will be compared to Welsh practices not participating in the study (those not consented and those not approached) to assess non-specific effects of taking part in a trial as well as the external validity of the trial.

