### Sample size

The SD of year-to-year within-practice changes in total dispensed antibiotic rates per 1000 patients between 2001 and 2002 was 70 items per 1000 patients in Wales. To detect a difference of 10% (73 dispensed antibiotics per 1000 patients) in the change in total antibiotic dispensing rate per annum between intervention and control practices, with 90% power, requires 21 practices per group. However, increasing this to 30 practices per group (approximately 80–90 clinicians per group) will allow a more robust exploration of a) practice characteristics and prescribing outcomes and b) the effect on resistance in urine samples: 25 practices per group will give 90% power to detect a reduction in resistance rates from the current 25% to 20% for Trimethoprim and from the current 6% to 3% for Cefalexin.

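### Primary ANCOVA omits two of the three balancing variables and the blocks; its standard error is overstated if these predict dispensing beyond prior prescribing

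*Protocol article*

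**What the plan says.** Protocol article, Randomization: allocation waits until all practices are recruited and is then constrained. The balancing variables are three-year average antibiotic prescribing, "practice size (number of whole time equivalent staff at recruitment) and proportion of GPs in the practice registered for the study". The section adds: "Practices will be sub-divided into three blocks and allocation balanced within each block". Within each set, the 1000 allocations with the smallest sum of squared standardized differences are kept, and one of them is drawn at random.

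Protocol article, Main analysis: the annual dispensing rate per 1000 patients is compared between arms "using analysis of covariance with the average of the previous three years' prescribing as a covariate". No other covariate and no block term is named for this model. Adjustment for further practice factors is placed among the exploratory analyses.

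Protocol article, Sample size: the SD of year-to-year change "between 2001 and 2002 was 70 items per 1000 patients in Wales". Detecting 73 items per 1000 "with 90% power, requires 21 practices per group", and the plan recruits 30 per group.

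**The concern.** Constrained allocation keeps the arms close on the balancing variables, so those variables contribute almost nothing to the sampling variation of the treatment difference. A model that leaves them out still counts the outcome variance they explain as residual error. The reported standard error then exceeds the true one. The same applies to blocks whose mean outcomes differ.

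Three things are at stake: wider confidence intervals than the design warrants, a test that rejects less than 5% of the time under the null, and some power. Interval width matters whatever the p-value, because the primary effect also feeds the cost-effectiveness ratio. The article says that admission and resistance rates will be compared in a similar way, so the omission may carry over to them. The resistance calculation has less slack, since it uses 25 of the 30 practices per group.

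**Working it through.** **Inputs from the protocol article.** Effect 73 items per 1000; SD 70; power 90%; 30 practices per group; three blocks; 1000 allocations kept per set; one covariate in the primary model.

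**Assumptions (not in the article).** Two-sided 5% test; equal blocks of 20 split 10:10; residual SD of 70 given prior prescribing; R² = share of that residual variance explained by the omitted variables, from 0 to 0.4.

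**1. The plan's own figure.** n per group = 2(1.96 + 1.2816)² × (70/73)² = 19.3, so 20 by the normal approximation. The t-test version gives 20.3, so 21. The stated 21 is reproduced. With 30 per group, t-test power for 73 items is 97.8%.

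**2. Tightness of the constraint.** C(20,10)/2 = 92,378 distinct splits per block. 1000/92,378 = 1.08% are kept, so the balance is close.

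**3. Analytic size.** With near-perfect balance, the reported SE is about 70 × √(2/30) = 18.1 and the true SE is about 18.1 × √(1−R²). The ratio is 1/√(1−R²):
- R² = 0: 1.00
- R² = 0.1: 1.054 (5%)
- R² = 0.2: 1.118 (12%)
- R² = 0.4: 1.291 (29%)

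Type I error is approximately 2[1 − Φ(c × ratio)], with c the two-sided 5% point of t on 57 df (2.00). This gives 3.5%, 2.5% and 1.0% at R² of 0.1, 0.2 and 0.4.

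**4. Simulation of the scheme.** Three blocks of 20, with 1,500 runs per setting. In each block, 20,000 of the 92,378 splits were examined and the best 216 kept (216/20,000 = 1.08%). One split was drawn and the arm labels were then randomized. Practice size and proportion registered together explain R². Full model means all three covariates plus block. The SE and SD columns come from the null runs.

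| R² | Reported SE, prior prescribing only | True SD of that estimate | Reported SE, full model | Type I error, prior only / full | Power at 73, prior only / full | Power at 55, prior only / full |
|---|---|---|---|---|---|---|
| 0 | 18.01 | 18.27 | 18.02 | 5.6% / 5.5% | 97.9% / 98.0% | 84.7% / 84.5% |
| 0.1 | 18.05 | 16.69 | 17.10 | 3.3% / 4.5% | 98.8% / 99.2% | 85.5% / 88.3% |
| 0.2 | 18.00 | 16.41 | 16.07 | 3.6% / 5.9% | 99.1% / 99.3% | 87.3% / 91.1% |
| 0.4 | 18.06 | 14.11 | 13.91 | 1.2% / 4.5% | 99.3% / 100% | 92.4% / 97.2% |

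The power difference at 55 items is 2.8, 3.8 and 4.8 points for R² of 0.1, 0.2 and 0.4. Monte Carlo error is about 0.6 points for type I error and 0.3 to 0.9 points for power. A repeat with 3,000 runs per setting gave type I errors of 4.0%, 2.8% and 1.0% for the prior-prescribing-only model.

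**5. Blocks.** With R² = 0.1 and block means shifted by −0.3, 0 and +0.3 SD, the prior-prescribing-only model reports an SE of 18.5 against a true 16.7. Its type I error is 2.9%, against 4.7% with block in the full model.

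**The case against.** The case for leaving the model alone has four parts.

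- **The omitted variables may add little.** The model already holds the outcome's own three-year average, probably its strongest predictor. The outcome is a rate per 1000 patients, so list size is in the denominator. Proportion registered mainly reflects how much of a practice would be trained; the article gives no reason why it should predict dispensing without the intervention.
- **A block effect is unproven.** Randomization follows full recruitment, so blocks need not be recruitment waves, and the article does not say how they are formed. They may exist only to make enumeration feasible.
- **The present analysis is valid.** The estimate is unbiased and the error is on the conservative side. The sample size takes no credit for balancing, so no power that the plan relied on is lost.
- **The statistical analysis plan is not shown** and may hold these terms.

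The first three parts stand, and they limit the point. A reader might infer that the standard errors are certainly too large. The documents do not support this: at R² of 0 the two models agree. A reader might also infer that the primary test falls short of its 90% power; at 73 items it does not in any setting examined.

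The fourth part does not remove the point. The article itself fixes the primary model with one covariate and makes other adjustment exploratory, so the stated model and the stated randomization do not match.

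**Conclusion.** The point holds conditionally. The primary model leaves out two of the three balancing variables and the blocks. If any of these predicts dispensing beyond prior prescribing, the reported standard error is overstated: by about 5% at R² 0.1, 12% at 0.2 and 29% at 0.4. The inference is then conservative, and no false-positive risk arises.

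The practical loss is in interval width and in power for effects smaller than planned. It is under 1 point at 73 items and about 3 to 5 points at 55 items. Smaller effects deserve attention here: the article reports a mean reduction of 6% from earlier interventions and grants that 10% could look ambitious.

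The mismatch is plain from the text. Its size rests on the assumed R², a residual SD of 70, equal blocks of 20 and a two-sided 5% test. This is a cheap improvement to a valid analysis and does not correct an invalid one.

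**What to change.** Specify the primary model as ANCOVA of the annual dispensing rate on arm, prior three-year prescribing, practice size (whole time equivalent staff), proportion of GPs registered, and block (two indicators). Keep the model with prior prescribing alone as a sensitivity analysis, optionally with a permutation test over the retained allocations.

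The change is about one sentence in the Main analysis section, and every variable is already held from randomization. It uses 4 more degrees of freedom: 60 − 3 = 57 residual now, 60 − 7 = 53 after. If the factors turn out not to be prognostic, almost nothing is lost (97.9% against 98.0% power at 73 items, 84.7% against 84.5% at 55). Fixing the model in advance also prevents a later choice between adjusted and unadjusted results.

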#### Qualitative analysis

We will employ standard thematic analysis techniques, where transcripts will be closely examined to identify themes and categories[55]. Codes will be applied to these broad themes which will then be broken down further into sub-codes. Agreement on concepts and coding will be sought between members of the research team in order to ensure reliability. A proportion of the data (10%) will be coded by two different team members to check on reliability of the coding scheme. The interviewing will be iterative, where new themes emerge we will incorporate them into the interviews. Thematic analysis will be supported by the use of computer-assisted qualitative analysis software (NVIVO8).

#### Cost effectiveness analysis

All resources will be valued using conventional methods[54]. Totals, means and confidence intervals for each training component will be identified, and analyzed using SPSS. Where costs are skewed, bootstrapped confidence intervals will be used.

The net cost of the intervention (likely to be positive) will be assessed against the primary outcome (reduction in dispensed oral antibiotics) to provide an incremental cost effectiveness ratio (ICER). Although there is a literature on the effectiveness of measures to improve antibiotic use, we could identify no comprehensive cost effectiveness analyses against which the above ICER can be compared. Accordingly the present study will not be able to provide evidence to show whether STAR is more or less cost effective than other measures with the same objective. It will, however, provide an evidence base for comparison in future studies.

## Discussion

This trial will be the first to evaluate the effectiveness of a theory-based intervention involving a blended learning program which focuses on both clinicians' reflections on their prescribing habits and practice level data on prescribing and antimicrobial resistance, as well as an introduction to novel consulting strategies for use during consultations for common infections. This approach has the potential to improve communication between clinicians and patients, as well as reducing unnecessary antibiotic prescribing. One recent study which focused on improving communication achieved an impressive 40% relative reduction in antibiotic prescribing at 12 months[56].

### Strengths

This study will be implemented in Wales and will include general practice surgeries from areas of high social deprivation as well as more affluent areas. We will use routine data as the main outcome which will enable us to compare practices taking part in the study with those outside the study. We will also be able to look at dispensing data both before and after the study to examine changes in behaviour.

Given that in the UK in recent years there has been a considerable reduction in inappropriate antibiotic prescribing, a reduction of 10% in antibiotic prescribing rates may seem optimistic. However, taking into account the findings of Welschen[16,33] and Altiner[56] and the fact that the UK has higher rates of antibiotic prescribing than both the Netherlands and Germany, and that the intervention we propose uses an innovative mix of approaches to behaviour change, we feel that this is nevertheless feasible.

The main outcome will not simply be antibiotic prescribing in a single consultation as in individually randomized trials[57], but rather, antibiotic prescribing for a whole year. This will allow for assessment of maintenance of skills and more powerful analyses that better assess the pragmatic effect of the intervention over time.

The cluster design will limit the chances of contamination. Once individual practitioners are trained in new consulting skills and are given new information about the indication and choice of antibiotic, they could not effectively revert back to their previous 'usual care' according to individual patient randomization. All participating clinicians in the same practice will be randomized to the same intervention condition to prevent contamination within practices.

### Protecting against bias

Practices who volunteer for the study are likely to be motivated to have access to the intervention, so those who are allocated to the control group may be disappointed. In order to avoid differential dropout between the experimental and control groups, we will offer those practices in the control group the opportunity to complete the training program after the one year follow-up period.

One important issue is whether clinicians will actually use the skills that they have learned in practice, since maintenance of these skills is challenging. Whilst the clinicians will learn the theory behind the communication skills and will learn to use the key strategies during consultations and appreciate the reasons for doing things this way, they might still not incorporate these into their routine practice. However, the intervention focuses on why change is important while at the same time enhancing clinicians' skills. The strategies taught will fit within the timescale of a routine consultation and this we hope will increase uptake. In addition, we will have a 'booster', which will consist of both on and offline elements to encourage maintenance of skills.

### Evaluations

The study will incorporate both an economic evaluation and a process evaluation. The process evaluation will allow us to explore the impact of different aspects of the intervention. If the trial does not show an effect it will allow us to explore possible reasons for this. In addition to estimating the overall cost of the intervention, the economic evaluation will identify its effect on consultation length as this is likely to be a factor of concern to clinicians which could affect its adoption. One challenge we face is measuring the impact of using the communication skills on consultation length. We plan to use the practice computer systems to provide an estimate of this, where possible.

The STAR Program grew out of seminal qualitative studies and intervention development research on clinician behaviour change. This study will therefore not simply make an incremental contribution. It will evaluate a unique, yet applicable, approach that has the potential to radically change research direction, clinical practice and policy. Since enhanced communication skills are the core of the intervention, beneficial effects on clinical practice are likely, not only in the management of common infections, but also in other clinical areas. The intervention is easily generalisable and could be rolled out using current technology and prescribing advisors to deliver the seminars. The intervention design using novel blended learning approaches will be applicable to continuing professional development in other clinical domains.
